#### Data management {19}

Trained and designated research team members will be responsible for entering research data which will be stored in a centralized, secure REDCap server [13, 14] at the CHU de Québec – Université Laval. The case report form will include range checks for data values and standardized input values for dates. A training session of an hour will be provided to each research team member by a single investigator (MH) to promote data quality. Each patient will be coded in the dataset to preserve confidentiality, and the key will only be available to the principal investigator (AD).

#### Confidentiality {27}

All research files including signed patient consents will be kept under lock and key in the ophthalmology clinical research department of the CHU de Québec – Université Laval and will only be available to authorized research team members. Trial participants will be assigned a code in the dataset to preserve confidentiality and the key will only be available to the principal investigator (AD). Nominal data will be destroyed 15 years after the conclusion of the study.

#### Plans for collection, laboratory evaluation and storage of biological specimens for genetic or molecular analysis in this trial/future use {33}

Samples of undiluted and diluted vitreous could be collected at the start of surgery as part of an ongoing biobank (Research Ethics Board number: 2021–5991) at our center independent of the current study. These would be transferred on ice to the laboratory where they will be stored in a dedicated refrigerator. Cytokine profiling could be performed on the samples using multiplex array kits as well as RPE cell quantification.

### Statistical methods

#### Statistical methods for primary and secondary outcomes {20a}

The primary outcome will be compared between the groups using the chi-square test for the difference in rates of SSAS in both the surgical technique and gas tamponade arms of the study. Testing between the groups for secondary outcomes of PHVA at 8–10 weeks and 6 months, final BCVA, final retina status (i.e., attached or detached), time to onset of RD recurrence, severity and number of complications, and questionnaire results will also be performed using adjustments for repeated measures and multiple comparisons as appropriate.

To calculate estimates of the treatment effects and their corresponding 95% confidence intervals (CI), a multiple logistic regression including both surgical technique and gas tamponade will be built for SSAS. Cox proportional hazards and multiple linear regression models will also be built for the time to onset of RD recurrence and final BCVA, respectively. In these analyses, we assume that there is a negligible interaction between surgical technique and gas tamponade. However, appropriate interaction terms will be added to the models to explore this possibility. If this shows negligible interaction, both analyses will be performed independently.

Statistical analyses will be performed using R for Windows (version 3.6.3; R Foundation for Statistical Computing) and IBM SPSS Statistics for Windows (version 27.0; IBM Corp., Armonk, NY). Analyses will be conducted at the 0.05 significance level, except when appropriate for adjustment of multiple comparisons.

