### Objectives {7}

The objective of this study is to analyze and compare the surgical outcomes, functional visual outcomes, complications, and quality of life associated with primary RRD repair using (A) PPV or PPV-SB (primary objective) and (B) SF_6_ and C_3_F_8_ gas tamponade (secondary objective). Our working hypotheses are as follows:PPV and PPV-SB have similar single-surgery anatomic success (SSAS) rate.PPV may lead to better final best-corrected visual acuity (BCVA), less complications, and better quality of life compared to PPV-SB.SF_6_ and C_3_F_8_ gas tamponades have similar SSAS rates, visual outcomes, complications, and quality of life.There is minimal to no significant interaction between surgical technique (i.e., PPV or PPV-SB) and gas tamponade (i.e., SF_6_ and C_3_F_8_).

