### Outcomes {12}

The primary outcome is SSAS defined as freedom from reoperation for recurrent RRD at all follow-up evaluations. Localized recurrences or new tears treated using a laser in the ambulatory clinic will not be considered a failure of the primary surgery but will be noted. We considered a difference of 10% in SSAS to be clinically relevant for this trial and based the sample size calculation on this threshold of chosen efficacy. Secondary outcomes will include PHVA at 8–10 weeks and 6 months, final BCVA, final retina status (i.e., attached or detached), time to onset of RD recurrence, severity and number of complications, and questionnaire results (see Additional file 1). The principal questionnaire was previously used and validated by Potic et al. [12] with additional questions used to specifically assess possible side effects and reductions in quality-of-life associated with the addition of SB and longer-duration intraocular gases. In cases of primary surgery failure, the cause of recurrence (i.e., PVR including epiretinal membrane (ERM) in the macular area causing recurrent RD, new or recurrent retinal breaks) will be reviewed. The extent of PVR at follow-up will also be evaluated. The duration of surgery will also be collected. Number of additional visits and supplementary laser and intraocular pressure treatments will be evaluated. Complications will be graded using the novel Classification of Ophthalmological Complications (COC; see Table 1).

**Table 1 Tab1:** Classification of ophthalmological complications (COC)

Complication grade	Definition
Grade I	Any deviation from the normal postoperative course without the need for modification of planned pharmacological treatment or surgical intervention Allowed therapeutic regimens are as follows: any previous medication, any medication prescribed routinely (i.e., topical antibiotics, glaucoma drops, anti-inflammatory drops, steroid drops, oral pills), artificial tears, hot compresses, and analgesic drugs (Advil/Tylenol only)
Grade II	Requiring change in planned pharmacological treatment with higher frequency or longer duration of drops or the introduction of new drugs (including autologous serum drops); these can include glaucoma drops and steroid drops and the use of oral drugs other than Advil/Tylenol (e.g., Diamox, prednisone). Also includes YAG capsulotomy

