### Sample size {14}

We based our sample size calculations on the size necessary to detect a clinically significant effect in surgical technique, given that estimates of effect size among gas tamponades are not as precise in the literature and are a secondary purpose of our study. Based on previous results from our center, SSAS is achieved in 92% and 88% of phakic patients undergoing PPV and PPV-SB, respectively, compared to 91% and 90% in pseudophakic patients. We therefore have at most a 4% difference between the treatment groups. In the PRO study reports, SSAS rates differed between PPV and PPV-SB with 83% and 91%, respectively, in phakic patients and 84% and 92% in pseudophakic patients. Based on our previous results, this would yield a small effect size of about 0.13, while this would be approximately 0.25 according to the treatment differences in the PRO study reports. Considering that a treatment difference smaller than what was found in the PRO study could be deemed not clinically significant, we are proposing a total sample size of 560 patients (*n* = 140 per group) which, assuming a 10% drop-off rate, would still allow us to detect an effect size of 0.25 with a power greater than 80% (see Table 3).

**Table 3 Tab3:** Total sample size calculation to detect an effect in the ranges of 0.20 to 0.30 for surgical technique (i.e., PPV and PPV-SB) at various study powers. We are proposing a sample size of 560 patients. Corresponding effect size and power will be achieved for the analysis of gas tamponades (i.e., SF_6_ and C_3_F_8_)

Effect size	Power		
	80%	85%	90%
0.20	784	900	1052
0.25	**504**	**576**	672
0.30	348	400	468

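### The protocol tests each factor unconditionally, then makes the independent factor analyses conditional on an interaction look with about 30% power at the design effect

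*Protocol article*

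**What the plan says.** All of the analysis text is in the protocol article, Statistical methods for primary and secondary outcomes {20a}. It makes four statements in this order.

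1. SSAS is compared by chi-square test for surgical technique and for gas tamponade. No condition is attached.
2. Treatment effects and 95% CIs for SSAS come from a logistic regression containing both factors. Cox and linear models are planned for time to recurrence and final BCVA.
3. The assumption behind the models is given: "In these analyses, we assume that there is a negligible interaction between surgical technique and gas tamponade". Interaction terms are to be added to explore whether it holds.
4. A condition follows: "If this shows negligible interaction, both analyses will be performed independently".

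The significance level is 0.05: "Analyses will be conducted at the 0.05 significance level, except when appropriate for adjustment of multiple comparisons".

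Objectives {7} lists the absence of interaction as a working hypothesis: "There is minimal to no significant interaction between surgical technique" and gas tamponade.

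Sample size {14} addresses main effects only: "we are proposing a total sample size of 560 patients", 140 per cell, with 10% drop-off, for an effect size of 0.25. The rates behind that effect size are these: "SSAS rates differed between PPV and PPV-SB with 83% and 91%, respectively, in phakic patients and 84% and 92% in pseudophakic patients". Outcomes {12} gives a different target: "We considered a difference of 10% in SSAS to be clinically relevant for this trial".

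**The concern.** Statements 1 and 4 cannot both govern. If the chi-square tests on the margins stand whatever happens, the independent analysis of the two factors is not conditional on anything. If it is conditional, the tests in statement 1 are not the fixed analysis they appear to be. As written, the team could look at the interaction estimate first and then decide whether the main-effect analyses go ahead as described.

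The quantity used for that decision is one the trial was not sized to estimate. In a balanced 2 × 2 design the interaction, taken as the difference between the two simple effects, has twice the standard error of a main effect. An interaction as large as the effect the trial seeks would more often than not be missed, so a finding of *negligible* would carry little information.

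Two things are at stake: whether the main-effect analyses are fixed before the data are seen, and whether the fourth working hypothesis can be supported by a test that would usually be non-significant even if the hypothesis were false.

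**Working it through.** **Inputs.** From Sample size {14}: 560 patients, 10% drop-off, so 560 × 0.9 = 504 evaluable, 252 per level of a factor and 126 per cell; target effect size 0.25. From {20a}: level 0.05. Sidedness is not stated; two-sided is taken because it reproduces Table 3. The interaction is defined as the difference between the effect of technique under one gas and its effect under the other.

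**Reproducing the plan's own figure.** The quoted rates give Cohen's h of 0.241 (83% v 91%) and 0.250 (84% v 92%), which matches the 0.25 used.
- n per level = 2 × (1.96 + 0.8416)² / 0.25² = 251.2, rounded up to 252. The total is 504, exactly the Table 3 entry for 80% power. All nine Table 3 entries come within 2 patients.
- Main-effect power at 504: Φ(0.25/√(4/504) − 1.96) = Φ(0.846) = 80.1%.

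**Interaction equal to the design effect, h scale.**
- SE = √(4/126) = 0.178, twice the main-effect SE of √(4/504) = 0.089.
- Power = Φ(0.25/0.178 − 1.96) = Φ(−0.557) = 28.9%. With all 560 evaluable it is 31.5%.
- For 80% power, N = 16 × (2.8016/0.25)², about 2,010 evaluable patients.
- At 504, an interaction twice the design effect would have 80% power.

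**Risk-difference scale, assuming SSAS near 90%, so p(1 − p) = 0.09.**
- SE of a main effect = √(2 × 0.09/252) = 2.7 points.
- SE of the interaction = √(4 × 0.09/126) = 5.3 points (0.0535).
- Power for 8 points = Φ(0.08/0.0535 − 1.96) = 32%.
- Power for 10 points = Φ(0.10/0.0535 − 1.96) = 46%.
- 95% CI half-width = 1.96 × 0.0535 = 10.5 points.

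**Sensitivity of the half-width to the assumed SSAS.** Over the 83% to 92% quoted in Sample size {14}:
- at 83%, 1.96 × √(4 × 0.1411/126) = 13.1 points;
- at 92%, 1.96 × √(4 × 0.0736/126) = 9.5 points.

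**Sensitivity of the power to scale and pattern.** Cell rates were built so that the difference of differences equals the target, with the effect present under one gas only or reversed between gases, on the risk and logit scales.

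| Target read as | 504 evaluable | 560 evaluable |
|---|---|---|
| 8 points (83/91% or 84/92%) | 24% to 33% | 26% to 36% |
| 10 points (82/92% assumed) | 33% to 46% | 36% to 50% |

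Simulation on the logit scale (200,000 runs per pattern, 83/91%, 504 evaluable) gave 23% to 28%, in line with the first row.

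**The case against.** The strongest reply is that the primary test is already fixed. The section opens with chi-square tests that carry no condition. The interaction sentences come in the next paragraph, which concerns effect estimates, and they describe the look as exploratory. On that reading the condition touches only the models. Much of this stands: a reader might infer that the data choose the primary analysis, and the document does not support so flat a statement. What it does support is a conflict between an unconditional test and a conditional sentence.

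A reader might also infer that a chance interaction would move the trial to comparisons among four cells, with a calculable loss of power or rise in false positives. The protocol names no alternative analysis, so any such figure would price a procedure that it does not contain. Nor does the word *independently* show that the other factor would be dropped: a model with both factors is already planned, and the word can mean assessing each factor at its margin.

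The protocol sets no p-value rule for *negligible* and does not say that a non-significant test will confirm the hypothesis. A threshold could properly sit in the SAP, and its absence here is not the complaint. The point is a decision rule that the protocol itself states.

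Finally, low interaction power is common to balanced 2 × 2 trials and contradicts no power claim made here. That is true. It matters only because the look has been given a deciding role.

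**Conclusion.** The point holds as a conflict within {20a} that leaves a data-dependent route to the main-effect analyses. The look is a weak basis for that choice: power is about 30% for an interaction equal to the design effect, about 33% to 46% if the 10 points of Outcomes {12} are the target, and the 95% CI half-width is about 10.5 points. That half-width is about as large as the difference the protocol calls clinically relevant, so a non-significant interaction could not support the fourth working hypothesis.

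These figures rest on 504 evaluable patients in equal cells, a two-sided 0.05 test where power is quoted, and SSAS near 90% for the half-width (9.5 to 13.1 points over 92% to 83%). The sample size for the main effects is not in question. The wording should be corrected before analysis; Trial status gives July 2027 as the approximate end of recruitment, so there is time.

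**What to change.** In {20a}, replace the conditional sentence with a statement that the marginal effect of each factor, from the two-factor model already planned, is primary whatever the interaction shows, so that it agrees with the unconditional chi-square tests. As supportive results, report the interaction in SSAS as a difference in risk differences with its 95% CI, together with the four cell rates. Judge the fourth working hypothesis by that interval, not by a non-significant p-value.

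The cost is wording only; sample size, conduct and data collection do not change. The downside is that, if a real interaction exists, each marginal effect is an average over the levels of the other factor. The four cell rates make that visible to the reader.

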#### Interim analyses {21b}

An interim analysis will be conducted in the middle of trial recruitment to verify that no statistically significant difference in SSAS is detectable. Should the difference be significant (> 10% between the groups) and place the patients in one of the groups at increased risk if recruitment is continued, the principal investigator (AD) reserves the right to make the final decision to terminate the trial.

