### Trial design {8}

This is a large, 2 × 2 factorial, interventional, randomized controlled trial. Eligible patients with primary RRD will be randomized using a simple randomization 1:1 to receive PPV or PPV-SB and SF_6_ or C_3_F_8_ gas tamponade. Statistical analyses of the outcomes will aim to demonstrate the superiority of one technique over the other.

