### Assignment of interventions: blinding

#### Who will be blinded {17a}

Outcome assessors, investigators, and data analysts will be blinded to the assignment of the interventions and the attributed code in the database until the end. For feasibility reasons, the trial participants and the clinical team including the treating surgeon will not be blinded to the intervention allocation. Blinding of the treating surgeon in relation to surgery technique will not be possible given that they will be responsible for adding the SB, and this will be visible on dilated fundus examination at follow-up given the scleral depression caused by the SB, while blinding to gas tamponade will not be feasible given that the gas bubble will dissipate at a faster rate with SF_6_ compared to C_3_F_8_ on follow-up examinations. As for trial participants, they are operated under local anesthesia with a retrobulbar block and sedation. They can therefore overhear surgeons discussing the next steps with the scrub nurse, deduce the addition of the SB based on duration of surgery, and see the speed at which the gas disappears from their visual field. 

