#### Composition of the data monitoring committee, its role and reporting structure {21a}

A data monitoring committee will not be required for this trial given that it will involve a relatively small number of patients and compare procedures that are already part of the standard of care.

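### The interim rule equates statistical significance with a gap above 10%, which are different criteria, and it sets no boundary, names no comparison and conflicts with the blinding section

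*Protocol article*

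**What the plan says.** The Protocol article's section {21b} on interim analyses opens with this plan: "An interim analysis will be conducted in the middle of trial recruitment to verify that no statistically significant difference in SSAS is detectable". The next sentence puts a difference of more than 10% between the groups in brackets as the meaning of significant. It adds that continuing must put one group at increased risk, and gives the principal investigator the last word, in that this role "reserves the right to make the final decision to terminate the trial".

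Four other sections bear on this:

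- Statistical methods {20a} sets the general level: "Analyses will be conducted at the 0.05 significance level, except when appropriate for adjustment of multiple comparisons". The primary test is the "chi-square test for the difference in rates of SSAS in both the surgical technique and gas tamponade arms of the study", so two sets of groups are compared.
- Trial design {8} gives the aim: "Statistical analyses of the outcomes will aim to demonstrate the superiority of one technique over the other".
- Section {17a}, on blinding, states: "Outcome assessors, investigators, and data analysts will be blinded to the assignment of the interventions and the attributed code in the database until the end".
- Section {21a}, on data monitoring, explains why there is no committee: "A data monitoring committee will not be required for this trial given that it will involve a relatively small number of patients".

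**The concern.** The interim section fixes a rule, so this is not a detail left for an analysis plan. As written, the rule has three faults.

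1. It treats a significance test and a threshold on the observed difference as one criterion. If they disagree at the planned size, whoever applies the rule must choose between them after seeing the data.
2. It does not say whether the groups are PPV versus PPV-SB, SF6 versus C3F8, or both. It gives no interim significance level and no adjusted final level.
3. It has an investigator act on a between-group result that the blinding section withholds from investigators and data analysts until the end.

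At stake are the type I error of the primary comparison and the credibility of a decision to stop or continue that different readings of the same sentence could justify.

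**Working it through.** **Inputs.** Total sample size: "we are proposing a total sample size of 560 patients" (Sample size {14}). Allocation is 1:1 on each factor (Trial design {8}). Centre SSAS rates are 88% to 92%; the PRO study's are 83% v 91% (phakic) and 84% v 92% (pseudophakic), a gap of 8 points each time (Sample size {14}). Assumptions: a two-sided test, an interim at half information, and a common SSAS of 90% as base case with 85% to 92% as the range.

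**The plan's own figure first.** Two-sided alpha 0.05, 80% power and standardized effect 0.25 give 252 per arm, 504 in total. This is the Table 3 entry, and 560 × 0.9 = 504. The two-sided 0.05 reading is therefore the plan's own.

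**Do the two criteria agree?** At mid-recruitment there are 560/2 = 280 patients, 140 per arm of each factor. The standard error of a difference under a common rate p is SE = √(2p(1−p)/140). The gap needed for p<0.05 is 1.96 × SE; a 10-point gap has z = 0.10/SE.

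| SSAS | SE | Gap at p<0.05 | z at 10 points | Two-sided p at 10 points |
|---|---|---|---|---|
| 92% | 0.0324 | 6.4 points | 3.08 | 0.002 |
| 90% | 0.0359 | 7.0 points | 2.79 | 0.005 |
| 88% | 0.0388 | 7.6 points | 2.57 | 0.010 |
| 85% | 0.0427 | 8.4 points | 2.34 | 0.019 |

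They do not agree. At SSAS 90%, an observed gap between 7 and 10 points is significant at 0.05 but does not exceed 10%. The 8-point PRO difference, on which the trial is sized, lies in this zone of disagreement when SSAS is about 88% or higher.

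**Type I error.** Interim and final z statistics at half and full information have correlation √0.5 = 0.707. These figures assume that the trial stops and a difference is declared whenever the criterion is met, with the final test at 0.05 otherwise.

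- Interim criterion p<0.05 (boundaries 1.96 and 1.96): overall 0.083 per factor; binomial simulation gives 0.081 to 0.083.
- Interim criterion above 10 points on one two-arm comparison: by simulation with 560 evaluable, about 0.051 at SSAS 90%, rising to 0.057–0.058 at 85%. The normal approximation gives 0.052 and 0.060; it is higher because it ignores that a gap of exactly 14/140 does not exceed 10%. With 504 evaluable the simulated values are 0.053 and 0.067.

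**Boundaries that hold 0.05.** O'Brien-Fleming at half information: z = 2.797 (p = 0.0052), then z = 1.977 (p = 0.048); overall 0.0500. At SSAS 90% this needs an observed gap of 2.797 × 0.0359 = 10.0 points. Haybittle-Peto: z = 3.29 (p = 0.001), then 1.96; overall 0.0502. At SSAS 90% this needs 3.29 × 0.0359 = 11.8 points.

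**Blinding.** The interim section requires the principal investigator to know the size of the SSAS difference and which group is worse off. The blinding section keeps investigators and data analysts blinded until the end and exempts only participants and the clinical team, including the treating surgeon. No monitoring committee stands between the analysis and the investigators. The sections cannot both be followed unless the principal investigator counts as clinical team, which the article does not say. Even then, the data analysts' blinding needs reconciling with an interim comparison by group.

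**The case against.** The best defence is that the explicit 10% threshold governs. On one two-arm comparison at SSAS 90% it is almost the same as an O'Brien-Fleming boundary, and the inflation is slight. The stop is also discretionary and needs a group at increased risk, so it is a safeguard against harm rather than an efficacy claim. Boundaries are often left to an analysis plan, which is not shown here.

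Much of this stands. It limits the size of the problem and rules out 8.3% as the plan's actual error rate. It does not rescue the wording: the same section sets out to look for a statistically significant difference, and the near-match with a formal boundary is an accident of SSAS 90% that weakens at 85%. A later document could add a boundary, but it would have to override this text.

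Stronger readings are tempting but unsupported:

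- A reader might apply 10% to every pair of the four treatment combinations, because the sample size section counts 140 per group. That is the least likely reading: the same section speaks of treatment groups when it contrasts PPV with PPV-SB, and the methods section compares the arms of each factor. The real ambiguity is which factor is meant.
- A reader might infer that the principal investigator's participant key reveals allocation, or that blinded investigators control reoperation. The key is described only as a confidentiality measure, and the treating surgeon and clinical team are openly unblinded.

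**Conclusion.** The concern holds: the interim rule is badly fixed as written and should be corrected, though it does not invalidate the design. The two criteria lead to different decisions for observed gaps of about 7 to 10 points at SSAS 90% (8.4 to 10 at 85%). Type I error per factor is at worst about 8.3%, reached only if every interim p<0.05 leads to stopping and a declared difference. With the 10% trigger on one two-arm comparison it is about 5.1% to 5.8% for SSAS 90% to 85% with 560 evaluable, and up to 6.7% with 504. If the right to stop is never used, the interim adds nothing to the 0.05. These figures assume half information at the interim. The conflict between the interim and blinding sections does not depend on any of them.

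**What to change.** Rewrite Interim analyses {21b} before the interim data are seen:

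1. Name one comparison, PPV versus PPV-SB, pooled over gas.
2. Replace the 10% trigger with a single formal boundary. Either O'Brien-Fleming (two-sided p<0.0052 at half information, final p<0.048), which roughly keeps the intended 10-point threshold at SSAS 90%; or Haybittle-Peto (p<0.001, final level about 0.05).
3. State the final significance level in Statistical methods {20a} to match.
4. Reconcile the section with Who will be blinded {17a}: say who runs the comparison, and have that analyst tell the blinded investigators only whether the boundary was crossed.

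The cost is protocol wording and a final level of 0.048 instead of 0.05 under O'Brien-Fleming. Haybittle-Peto leaves the final level essentially unchanged but needs a larger interim gap, about 11.8 points at SSAS 90%. The sample size stays as it is.
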